
### The NEOVASC study

The NEOVASC study is a multicentric, prospective, randomized, controlled, open, and parallel group clinical trial conducted in four Austrian tertiary neonatal care facilities (Medical University of Innsbruck, Paracelsus Medical University Salzburg, Medical University of Vienna, Academic Teaching Hospital Feldkirch). The purpose of the present trial is to investigate the superiority of a prolonged (until 36 weeks’ gestation) exclusive human-milk-diet devoid of bovine-milk-based food components on cardiovascular and metabolic risk factors. By following formerly preterm infants until the corrected age of 5 years, we intend to facilitate research findings on the impact of specifically targeted early dietary interventions on long-term cardiovascular health. Previous research has shown that increases in BP [30, 31], alterations in glucose homeostasis [30, 32, 33], and vascular integrity [21] are visible even in early childhood following preterm birth. Given the inverse correlation between gestational age and adulthood diabetes [20] and hypertension [13, 18], respectively, we anticipate markedly significant results should our intervention in these preterm infants prove effective.

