### Randomization, study groups, and interventions

Randomization of preterm infants will be done electronically by the use of permuted blocks (block size = 4) within a stratified randomization. The allocation sequence will be generated by the study’s statistician and provided to the principal investigators in the form of a conventional unblinded randomization table. Stratification variables are the study site and birth weight (< 1000 g and 1000–1250 g). On the basis of ethical considerations, twins are always randomized into the same study group. Preterm neonates will be randomized to either (i) an exclusive human-milk-based diet composed of mother’s milk or pasteurized donor human milk in combination with a human-milk-based fortifier (Humavant^TM^ +4,+6; Prolacta Bioscience, Inc.) until 36 weeks of gestation (Randomized Study Product Group) or (ii) mother’s milk or pasteurized donor human-milk (as long as available) in combination with a human-milk-based fortifier (as long as human milk is available) until 32 weeks’ gestation and thereafter mother’s milk or pasteurized donor human milk with a bovine-milk-based fortifier or preterm formula (Randomized Control Group) in a 1:1 ratio. Feeding will be done by protocol in which fortification will begin when the infant is receiving 80–100 ml/kg/day of enteral nutrition. After 36 weeks’ gestation, human milk with a bovine-milk-based fortifier or preterm formula will be used in both groups. While blinding of study groups is always desirable in randomized studies, this is not possible for this study due to the nature of the intervention. As a control group, term-born age-matched infants will be included (Term-born Control Group). Infants within this control group will be recruited in kindergartens at 5 years of age. The results of the present study will further be compared to a group of very preterm infants enrolled for prior clinical studies at the Medical University of Innsbruck (Historical Control Group) [21, 30, 34]. See Figure S1 for a graphic display of the study design. The description of the overall study design is in agreement with the 2013 SPIRIT checklist (see Fig. 1).

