### Study outcomes and follow-up

Outcomes include predictors and intermediate components of cardiovascular disease. Primary outcomes include assessments of the absolute difference in fasting blood glucose levels, blood pressure levels, and the distensibility of the descending aorta using validated echocardiographic protocols [21, 35] at 5 years of age. Secondary outcomes include assessments of fasting blood glucose levels and blood pressure levels at 1 and 2 years of corrected age as well as comparisons of body mass index and lipid profiles at 5 years of corrected age. Data on the clinical status of preterm infants in the study will be obtained at baseline during hospitalization as well as at routine follow-up visits at 1, 2, and 5 years of age, respectively. See Fig. 1 (SPIRIT figure) for a summary of all essential study procedures in the preterm study participants. Data from participants within the term-born control group will be obtained during a singular visit at 5 years of age. Data about birth and postnatal development from these participants will be taken from the mother-child-pass (official Austrian medical records on pregnancy, birth, and early childhood). In addition, cord blood, milk, stool, and urine samples will be obtained from preterm study participants at various points during the study. While milk samples will be used for analyses regarding osmolarity and nutritional values, all other samples will be stored at − 80° C for post-study analyses. As for preterm study participants from the Medical University of Vienna, body composition using body plethysmography (Pea Pod®) will further be measured at term-equivalent and 3 and 6 months of corrected age, respectively.

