### Data management

Relevant data will be obtained using an electronic data capture system. After data acquisition is completed, a clean data file for the following statistical analyses will be established and stored. All investigators were trained with the electronic data system and regular monitoring visits are held to ensure proper data quality. Data management will be done by [name] and [name] Forwarding of patient-related data for further statistical analyses will only be done in pseudonymized or anonymized form. The code which enables the pseudonymized data to be allocated to a particular individual will be stored at the respective study centers. Following the completion of statistical analyses, data will be stored for 15 years in accordance with the “International Conference of Harmonization – Good Clinical Practice (ICH-GCP)” guidelines. All data will be handled in accordance with the EU General Data Protection Regulation and/or applicable national data protection regulations. Parents of study participants will be informed about their data protection rights in the informed consent form and written consent will be obtained.

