## Trial status

Protocol Version 4.7 (19 May 2020)

Trial status: Recruiting (first patient on 7 October 2020)

Study duration: Recruitment period of 36 months, follow-up until 5 years of age.

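### The reason given for not blinding covers the feeding period to 36 weeks, not blood pressure and echo measurement at 5 years, and the article provides no assessor masking

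*Protocol article*

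**What the plan says.** Under The NEOVASC study, the design is described as a "multicentric, prospective, randomized, controlled, open, and parallel group clinical trial".

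Under Randomization, study groups, and interventions, blinding of the study groups is called desirable, but "this is not possible for this study due to the nature of the intervention". No other reason is given. The same section says that the allocation sequence is "provided to the principal investigators in the form of a conventional unblinded randomization table". It also says that after 36 weeks' gestation human milk with a "bovine-milk-based fortifier or preterm formula will be used in both groups".

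Under Study outcomes and follow-up, the primary outcomes are fasting glucose, blood pressure and "the distensibility of the descending aorta using validated echocardiographic protocols [21, 35] at 5 years of age". Trial status likewise gives "follow-up until 5 years of age".

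No section shown mentions masked assessors, masked or central reading of echo images, or a procedure for measuring blood pressure. No section says who carries out the 5-year visit.

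**The concern.** The stated reason concerns the feeding. Ward staff prepare and give the feeds and parents see them, so neither can sensibly be masked up to 36 weeks. The primary outcomes are taken about five years later, long after the feeding policies have become the same. Nothing about the intervention then prevents the person who measures blood pressure, or who measures aortic diameters on an image, from being unaware of the arm. The sentence uses a reason that is valid for one period to dispose of blinding altogether.

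What is at stake is differential measurement error. Echo distensibility depends on where the reader places the vessel wall. Blood pressure depends on the observer to a degree set by the device and by the rule for accepting readings. The trial tests superiority, so expectation has a direction. If an assessor knows the arm, even a small shift in reading is counted as an effect of diet. Neither randomization nor anything in the analysis section (multiple imputation, the Benjamini-Hochberg procedure, the per-protocol analysis) can separate the two.

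**Working it through.** **1. Does the stated reason reach the measurement?**

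| Step | When | Can the feeding reveal the arm? |
|---|---|---|
| Randomized feeding | up to 36 weeks' gestation | Yes, to staff and parents |
| Common feeding policy | after 36 weeks' gestation | No difference in policy between arms |
| Blood pressure and echo (primary) | 5 years | Not through the intervention itself; only through records, the allocation table or parents |

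The remaining routes at 5 years are matters of access and communication, which can be controlled. They are not consequences of the nature of the intervention.

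**2. Reproducing the plan's sample size, to fix the scale.**

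Inputs from Sample size and statistical analyses: standardized effect 0.4, power 0.8, significance level 0.05, two-sample t-test, 100 per arm. Sidedness is not stated; two-sided is assumed.

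- n per arm = 2 × (1.960 + 0.842)² / 0.4² ≈ 98.1, rounded up to 99. The t-test version gives 99.1, rounded up to 100.
- Power at 100 per arm is 0.804 (t-test) or 0.807 (normal).
- A one-sided test would need 78 per arm, which does not match.

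The plan's 100 per arm is reproduced with a two-sided test.

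**3. Implied spread and standard error.**

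The standard deviations are not stated. They follow if the effect size of 0.4 applies to each outcome.

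- Systolic blood pressure: 102 − 99 = 3 mmHg; SD = 3 / 0.4 = 7.5; SE of the difference = 7.5 × √(2/100) = 1.06 mmHg.
- Distensibility: 85 − 76 = 9 units; SD = 9 / 0.4 = 22.5; SE = 22.5 × √(2/100) = 3.18 units.

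**4. Effect of an assumed differential reading error when the diet has no effect.**

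Let b be the error between arms and λ = b / SE. The two-sided type I error is 1 − Φ(1.960 − λ) + Φ(−1.960 − λ). Because b is set as a fraction of the target effect, λ = fraction × 0.4 / √(2/100), the same for both outcomes.

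| Error as share of target | Blood pressure (mmHg) | Distensibility (units) | λ | Type I error |
|---|---|---|---|---|
| none | 0 | 0 | 0 | 0.050 |
| 10% | 0.3 | 0.9 | 0.28 | 0.059 |
| 20% | 0.6 | 1.8 | 0.57 | 0.087 |
| 33% | 1.0 | 3.0 | 0.94 | 0.156 |
| 50% | 1.5 | 4.5 | 1.41 | 0.293 |

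In the 33% row, 0.155 of the 0.156 lies in the direction of the bias, against 0.025 without bias.

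These are unadjusted rates for one outcome with all 100 children per arm measured. With fewer children measured at 5 years the SE would be larger, and the same absolute error would inflate the rate less.

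**The case against.** The strongest reply is that the sentence speaks of blinding the study groups and stands among the feeding rules. An open trial can still have masked assessors, and the full protocol (version 4.7), the supplementary material or the cited echo protocols, none of them shown, may provide for this. Who measures, and what the electronic forms display, are details that an article often leaves out.

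Much of this stands. A reader might infer that the article forbids assessor masking, or that the staff who hold the allocation table also take the 5-year readings. The documents support neither: the table goes to the principal investigators, and the assessors are not identified. A reader might also infer that blood pressure is read by ear and so strongly depends on the observer. The device is not stated, and with an automated one the observer component would be small. The Data management statement that "Forwarding of patient-related data for further statistical analyses will only be done in pseudonymized or anonymized form" settles nothing either way, because it concerns transfer for analysis after measurement.

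The reply does not remove the point. The article does more than stay silent on masking: it states a design decision with a reason, without limiting it to those who feed or see the feeding, and calls the trial open. The reason does not extend to outcome measurement, and a reader who follows the text as published has no instruction to mask anyone.

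**Conclusion.** The point holds in limited form. The reason given for not blinding does not cover blood pressure and aortic distensibility at 5 years, the text shown provides no assessor masking, and two of the three primary outcomes are therefore left open to observer bias that could largely be avoided. How exposed blood pressure is depends on a device and procedure that are not described.

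The size cannot be derived from the documents. The range of about 5.9% to 29% rests on assumed errors of 10% to 50% of the target effect, on SDs implied by an effect size of 0.4, and on a two-sided test with 100 per arm. It also treats blood pressure and echo as equally susceptible, which they need not be. A reader might take the 15.6% at one third of the target as the trial's false-positive rate. It is not: no passage supports that particular error, and the figure ignores the planned Benjamini-Hochberg adjustment. Nor do the documents show that biased reading will occur.

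The change is worth making because it is cheap and the analysis cannot repair the problem afterwards. The first patient entered on 7 October 2020, so no 5-year measurement had been taken when the article appeared in July 2021.

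**What to change.** In Randomization, study groups, and interventions, limit the statement that blinding is not possible to caregivers and parents. Under Study outcomes and follow-up, add for the randomized comparison that:

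- 5-year blood pressure and echo are acquired by existing staff who have no access to the allocation table, with the arm field hidden in the electronic data capture forms they use;
- echo clips are stored under the study code and measured without arm label;
- any unmasking of an assessor is recorded.

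If the full protocol already provides for this, a sentence in the article saying so is enough.

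The cost should be small: an access setting, a work instruction and a code on the stored clips, with no change to sample size and no extra staff. Staffing at the sites is not described, so this is a judgement. The downside is that masking will be imperfect. Parents know the arm and may mention it, although coded reading of stored clips is largely protected from that. Masking cannot be extended to the historical controls, who were enrolled in prior studies, and is harder for the term-born children, who are recruited separately in kindergartens.

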**Fig. 1 Fig1:**
[figure not shown]
Standard Protocol Items: Recommendation for Interventional Trials (SPIRIT) figure of enrollment, intervention, and follow-up of preterm study participants

### Study outcomes and follow-up

Outcomes include predictors and intermediate components of cardiovascular disease. Primary outcomes include assessments of the absolute difference in fasting blood glucose levels, blood pressure levels, and the distensibility of the descending aorta using validated echocardiographic protocols [21, 35] at 5 years of age. Secondary outcomes include assessments of fasting blood glucose levels and blood pressure levels at 1 and 2 years of corrected age as well as comparisons of body mass index and lipid profiles at 5 years of corrected age. Data on the clinical status of preterm infants in the study will be obtained at baseline during hospitalization as well as at routine follow-up visits at 1, 2, and 5 years of age, respectively. See Fig. 1 (SPIRIT figure) for a summary of all essential study procedures in the preterm study participants. Data from participants within the term-born control group will be obtained during a singular visit at 5 years of age. Data about birth and postnatal development from these participants will be taken from the mother-child-pass (official Austrian medical records on pregnancy, birth, and early childhood). In addition, cord blood, milk, stool, and urine samples will be obtained from preterm study participants at various points during the study. While milk samples will be used for analyses regarding osmolarity and nutritional values, all other samples will be stored at − 80° C for post-study analyses. As for preterm study participants from the Medical University of Vienna, body composition using body plethysmography (Pea Pod®) will further be measured at term-equivalent and 3 and 6 months of corrected age, respectively.

### Sample size and statistical analyses

A group size of 100 preterm infants per study arm is sufficient to detect a lowering in systolic blood pressure from 102 mmHg (Randomized Control Group) to 99 mmHg (Randomized Study Product Group), a reduction of fasting glucose levels from 84 to 78.5 mg/dl, and an increase in the distensibility of the descending aorta from 76 to 85 kPa^−1^ × 10^−3^, respectively. Based on previous experience, the principal investigators are confident to recruit the intended number of study participants within a recruitment period of 36 months. Each of these calculations was performed considering a power of 0.8 by the use of two-sample *T*-test for independent samples with homoscedastic variances. The effect size for this clinical trial was based on Cohen’s *D* assuming an effect size of 0.4. All statistical analyses will be performed on an intention-to-treat paradigm with a significance level of 0.05. Multiple outcomes will be handled using the Benjamini-Hochberg procedure for controlling the false discovery rate. Distensibility and stiffness index β of the descending abdominal aorta and lipid profiles will be compared between groups with two-sample *T*-tests or the Wilcoxon rank-sum test as a primary analysis at any given time point (looking at change from baseline). However, an adjusted analysis using a general linear model will incorporate the potential time trends in the results, as well as relevant covariates. Relationships between elasticity and stiffness, or lipid profiles and independent variables (sex, gestational age at birth, birth weight, ponderal index) will be studied by univariate and multivariate regression analysis. Missing data will be imputed using a multiple imputation with chained equations approach. In the event of repeated missing data over time, the simplistic last value carried forward approach may be used. However, in order to evaluate the data from a sensitivity analysis perspective, a secondary analysis on a per-protocol basis will be performed. This analysis will only consider participants who were correctly randomized and have complete data sets.

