**Methods:**

The NEOVASC study is a multicentric, prospective, randomized, controlled, open, and parallel group clinical trial conducted in four Austrian tertiary neonatal care facilities. The purpose of the present trial is to investigate the effects of a prolonged exclusive human-milk-diet devoid of bovine-milk-based food components on cardiovascular and metabolic risk factors at 1, 2, and 5 years of corrected age. Primary outcomes include assessments of fasting blood glucose levels, blood pressure levels, and the distensibility of the descending aorta using validated echocardiographic protocols at 5 years of corrected age. The test group, which consists of 200 preterm infants, will therefore be compared to a control group of 100 term-born infants and a historical control group recruited previously.

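### The stated power of 0.8 with 100 infants per arm assumes complete 5-year data and an unadjusted 0.05, so it does not describe the planned analysis

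*Protocol article*

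**What the plan says.** All from the protocol article.

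- **Sample size and statistical analyses**, size claim: "A group size of 100 preterm infants per study arm is sufficient to detect a lowering in systolic blood pressure from 102 mmHg" to 99 mmHg, a fall in fasting glucose from 84 to 78.5 mg/dl, and a rise in distensibility from 76 to 85 kPa⁻¹ × 10⁻³.
- Same section, basis: "Each of these calculations was performed considering a power of 0.8", with a two-sample t-test for equal variances, "assuming an effect size of 0.4", and a significance level of 0.05.
- Same section, multiplicity: "Multiple outcomes will be handled using the Benjamini-Hochberg procedure for controlling the false discovery rate".
- Same section, missing data: chained-equations multiple imputation, possibly last value carried forward, and a per-protocol analysis restricted to complete data sets.
- Same section, recruitment: "the principal investigators are confident to recruit the intended number of study participants within a recruitment period of 36 months". The abstract gives the total: "The test group, which consists of 200 preterm infants".
- **Trial status**: "Recruitment period of 36 months, follow-up until 5 years of age". The primary outcomes are assessed at 5 years.
- **Informed consent procedure and withdrawal**: withdrawal is possible at any time, and data collection then stops.

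The size calculation mentions neither attrition nor the multiplicity adjustment. The article gives no attrition rate.

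**The concern.** A size calculation should describe the analysis that will be run on the infants who will be measured. Here it describes a single test at an unadjusted 0.05 on every randomized infant. The plan around it foresees a step-up adjustment over several outcomes and incomplete data after 5 years in infants of 500–1250 g at birth. Both omissions lower power, and they compound.

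The stake is interpretation. A non-significant primary outcome will be read against a claimed 80% chance of detecting the target difference. If the real chance is nearer 60–75%, that reading gives a null result more weight than it can bear.

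**Working it through.** **Inputs.** From the article: n = 100 per arm, 1:1 allocation, d = 0.4, significance level 0.05, power 0.8, two-sample t-test, three named target differences, Benjamini-Hochberg. Assumed: a two-sided test (not stated), the three primary outcomes as the adjustment family, between-outcome correlation of 0 to 0.6, and loss of 10% or 20%.

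**1. Reproduce the stated figure.** The noncentrality is d·√(n/2) = 0.4 × √50 = 2.83 on 198 degrees of freedom.

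- Required n for power 0.80: 99.08, hence 100 per arm.
- Power at n = 100: 0.8036. At 99: 0.7997. At 98: 0.7956.
- A one-sided test would need about 78 per arm, so it does not fit.

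The article's figure is therefore right on its own inputs. The margin is under 1%, and losing one infant per arm takes power just below 0.80. No allowance for loss or multiplicity can be hidden in a number that equals the uninflated requirement.

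**2. Recruited or completing?** 2 × 100 = 200, which is the total in the abstract and the number the recruitment sentence refers to. So 100 per arm is the number enrolled.

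**3. Loss alone, unadjusted 0.05.** Same formula with n = 100 × (1 − loss):

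- 10%: n = 90, power 0.76
- 20%: n = 80, power 0.71

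**4. Benjamini-Hochberg.** With three outcomes the ordered p-values are compared with 0.05 × 1/3 = 0.0167, 0.05 × 2/3 = 0.0333 and 0.05. No threshold exceeds 0.05, so power per outcome cannot exceed the unadjusted value. Because the procedure steps up, the cost depends on how many effects are real. Simulated t-tests (at least 200,000 replicates per setting; ranges span the correlations, and the second decimal is approximate) give, per truly affected outcome:

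| Assumed loss | All three effects d = 0.4 | Two | One |
|---|---|---|---|
| 0% | 0.77–0.78 | 0.72–0.73 | 0.66–0.67 |
| 10% | 0.72–0.73 | 0.67–0.68 | 0.61 |
| 20% | 0.66–0.67 | 0.61–0.62 | 0.54–0.55 |

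A check on the last column: a plain t-test at 0.0167 has power 0.661 at n = 100 and 0.545 at n = 80, which is the floor for the single-effect case.

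**5. Detectable differences.** The target differences and d = 0.4 imply SDs of 3/0.4 = 7.5 mmHg, 5.5/0.4 = 13.75 mg/dl and 9/0.4 = 22.5 units. At unadjusted 0.05 and 80% power, the detectable d is close to 0.4 × √(99.08/n):

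- n = 90: d = 0.420, or 3.1 mmHg, 5.8 mg/dl and 9.4 units
- n = 80: d = 0.445, or 3.3 mmHg, 6.1 mg/dl and 10.0 units

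Under Benjamini-Hochberg they are larger again, by an amount that depends on how many effects are real.

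**The case against.** **The figure is correct as computed.** This stands. A reader might infer an arithmetic error, but 100 per arm follows from the stated inputs. The fault is in what those inputs leave out.

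**No attrition rate is given, so every loss figure is an assumption.** This also stands. Death appears in the Safety section as part of a definition of serious events, not as an expected frequency, and investigators may exclude infants unlikely to survive the study period. The article does not establish how many will be lost. Still, it plans imputation and a complete-data analysis, and there is no margin for any loss. The multiplicity gap needs no loss assumption at all.

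**The multiplicity cost is small under the design alternative.** The article gives target differences for all three outcomes. If all three are real, the cost with full follow-up is only 2–4 points, and power for at least one significant primary outcome is 0.87–0.97. It is tempting to lead with 0.66, or with detectable differences at 0.0167. The first assumes that two of the three target effects are absent. The second describes a Bonferroni rule, which is not the planned one. But the claim is made for each outcome separately, and even the favourable case is below 0.8.

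**Imputation may recover information.** This stands in part. Glucose and blood pressure are also measured at 1 and 2 years, so the completer-based powers may be somewhat pessimistic for them. No earlier distensibility measurement is listed among the outcomes.

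**This is a condensed article.** The exact adjustment family may be defined in the full protocol or analysis plan, so its absence here is no fault. The power claim itself is stated in the article and can be judged there.

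**Conclusion.** The concern holds in this form: 100 per arm is the uninflated requirement for one unadjusted two-sided test and is also the number recruited, so 0.8 is not the power of the planned analysis.

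What follows from the document, given a family of the three primary outcomes and a two-sided test, is a modest shortfall if all three effects are real and data are complete, and one of about 13 points (0.80 to 0.66–0.67) if only one effect is real. What rests on assumed loss is the further fall, by roughly 5 points at 10% and 11–12 points at 20%. A larger family would lower the single-effect case: with four tests and full follow-up it is about 0.63.

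The document does not support calling the calculation wrong, treating any particular loss as fact, or presenting the single-effect case as the expected one.

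**What to change.** Keep 200 infants and restate the claim in the sample size section:

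- Say that 100 randomized per arm gives power 0.8 per outcome only with essentially complete 5-year data and an unadjusted two-sided 0.05.
- Give the power under the planned Benjamini-Hochberg procedure for a stated range of assumed loss, for example 0–20%, and for one, two or three real effects, as in the table above.
- Give the matching detectable differences for systolic blood pressure, glucose and distensibility, and say whether they rest on completers or on imputed data.

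The cost is text and a short simulation. No infants are added and no analysis changes. The drawback is that the stated power becomes less favourable.

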### Safety

Preterm infants, and especially those born very and extremely premature, are an exceptionally vulnerable and often seriously ill patient population. Many adverse events (AEs) seen in this collective may be of serious nature. However, most of these AEs are expected to occur with no relationship to the intervention performed during the NEOVASC trial. In addition, the use of human milk and a human-milk-based fortifier (Humavant^TM^) in preterm infants is based on years of prior experience in clinical routine. Given that this is a nutritional study using a routinely used feeding product in the absence of pharmacological interventions, the investigators decided to move forward without an independent “Data Safety and Monitoring Board (DSMB)” prior to the study’s initiation and an interim analysis or stopping guidelines were not included in the current study design. AEs may be defined as medical NEC, confirmed late-onset sepsis as identified by positive blood cultures and feeding intolerance resulting in NPO status ≥ 24 h, change to infant formula, bloody stools, bilious emesis, or severe abdominal distension that results in a change with clinical nutritional management of the patient. Severe adverse events (SAEs) may be defined as death, surgical NEC, and lengthening of hospitalization. All SAEs and suspected unexpected serious adverse reactions (SUSARs) will be reported to the respective local ethics committee. If in the opinion of the attending physician there is a reasonable likelihood that any AE may have been causally associated with products from Prolacta Bioscience, Inc., or if the event results in a death regardless of the likelihood of association, Prolacta Bioscience, Inc., will additionally be notified and further clinical actions will be taken depending on the nature of the incident and the certainty of their causal relationship to the study product or study-specific procedures, respectively.

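### The last-value-carried-forward fallback is not barred from the 5-year primary outcomes, so a toddler's blood pressure or glucose could be entered as the 5-year value

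*Protocol article*

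**What the plan says.** All of the missing-data rules stand in the protocol article under *Sample size and statistical analyses*. The general rule is "Missing data will be imputed using a multiple imputation with chained equations approach". The next sentence adds a fallback: "In the event of repeated missing data over time, the simplistic last value carried forward approach may be used". The fallback is not confined to secondary outcomes or to earlier visits, and nothing says how to choose between the two methods. The same section states "All statistical analyses will be performed on an intention-to-treat paradigm with a significance level of 0.05". It names one sensitivity analysis, a per-protocol analysis of correctly randomized children with complete data.

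Under *Study outcomes and follow-up*, the primary outcomes are fasting glucose, blood pressure and aortic distensibility at 5 years. For two of these an earlier value exists: "Secondary outcomes include assessments of fasting blood glucose levels and blood pressure levels at 1 and 2 years of corrected age". No distensibility measurement before 5 years is listed among the outcomes.

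**The concern.** A child seen at 1 year who then misses the 2- and 5-year visits is a plain case of repeated missing data. Under the fallback, that child's 1-year blood pressure or glucose may stand as the 5-year primary value. On a looser reading a 2-year value could be used in the same way, for example when the 1- and 5-year visits were missed.

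Both measures change as a child grows, so the carried value describes a different age. The method also fills in one value as if it were known and ignores the uncertainty about what it would have been at 5 years. If the arms lose children at different rates, age alone produces a difference between them. If the diet acts later than the carried visit, the treatment effect is diluted.

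The word *may* adds to the problem. In an open trial it leaves two methods available for a primary outcome with no rule for choosing. The three primary outcomes could also end up handled differently, because distensibility has nothing to carry.

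**Working it through.** **1. The plan's own sample size.** The inputs are in *Sample size and statistical analyses*: "A group size of 100 preterm infants per study arm is sufficient to detect" 102 versus 99 mmHg systolic; "Each of these calculations was performed considering a power of 0.8"; "assuming an effect size of 0.4"; significance level 0.05. Sidedness is not stated, and two-sided is assumed.

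- Normal approximation: n = 2 × (1.960 + 0.842)² / 0.4² = 98.1, so 99 per arm. The exact t-test gives 99.08, so 100 per arm, with power 0.804 at 100. The stated figure is reproduced. (One-sided would need only 78.)
- Implied SD for systolic pressure: 3 / 0.4 = 7.5 mmHg.
- The number holds only if every child contributes a 5-year value. With 80 observed per arm (20% missing, assumed), t-test power at d = 0.4 is 0.71.

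**2. What carrying forward does to the estimate.** Let

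- D = true difference at 5 years, study minus control
- E = difference at the carried visit
- g = amount by which the carried-visit control mean lies below the 5-year control mean
- p_S, p_C = shares carried forward in the study and control arms

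Each arm's mean is a mixture of 5-year and earlier values, so

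expected estimate = (1 − p_S)·D + p_S·E − g·(p_S − p_C).

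D = −3 mmHg is the plan's target. The values of g, p_S, p_C and E are assumptions; the documents give none of them.

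| Case | p_S, p_C | D, E | g = 5 | g = 8 |
|---|---|---|---|---|
| No effect, more carried in control | 15%, 25% | 0, 0 | +0.5 | +0.8 |
| No effect, more carried in study | 25%, 15% | 0, 0 | −0.5 | −0.8 |
| Equal shares, no early effect | 20%, 20% | −3, 0 | −2.40 | −2.40 |
| More carried in control, no early effect | 15%, 25% | −3, 0 | −2.05 | −1.75 |
| More carried in study, no early effect | 25%, 15% | −3, 0 | −2.75 | −3.05 |
| Equal shares, full early effect | 20%, 20% | −3, −3 | −3.00 | −3.00 |

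For example, row 4 with g = 5 is 0.85 × (−3) − 5 × (0.15 − 0.25) = −2.55 + 0.50 = −2.05. The spurious 0.5 to 0.8 mmHg is 17% to 27% of the 3 mmHg target (0.5/3 and 0.8/3).

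The same dilution applies to glucose. With equal 20% shares and no early effect, the planned 84 − 78.5 = 5.5 mg/dl would be estimated as 0.8 × 5.5 = 4.4 mg/dl.

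**3. Power and type I error.** These use a two-sample z-test, 100 per arm, SD 7.5 at each age, and arm variance 7.5² + p(1 − p) × (gap between the arm's two means)². With complete data this approximation gives power 0.807.

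| Gap g (mmHg, assumed) | 5 | 10 | 15 |
|---|---|---|---|
| Power, 20% carried in both arms, no early effect | 0.60 | 0.54 | 0.45 |
| Power, 20% carried in both arms, full early effect | 0.78 | 0.70 | 0.60 |
| Type I error, 10% versus 20% carried | 0.074 | 0.137 | 0.211 |

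With equal shares and no true effect, the type I error stays at 0.05.

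With no early effect, carrying forward does worse than analysing only the 80 observed children per arm (0.60 or less against 0.71). With the full effect already present and a 5 mmHg gap it does better than that (0.78), though still below complete data.

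**The case against.** The strongest reply is that this is an optional fallback. Multiple imputation is the rule. A child missing only the 5-year visit would naturally fall under it, and the fallback needs repeated gaps plus an earlier observed value. The shares in the tables are children actually carried forward, a subset of all losses, so 15% to 25% is a demanding assumption. Bias is not inevitable: with equal shares and an early effect equal to the 5-year effect the estimate is unbiased, and swapping the arms brings it to −2.75 to −3.05 against a true −3.0. The complete-data analysis supplies an estimate free of carried values.

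Most of this stands and limits the point to a possible bias of unknown size. Two parts do not remove it. The complete-data analysis changes the population as well as the handling of gaps, so it does not test the carried-forward assumption in the intention-to-treat set. And the point does not rest on silence: the article states the permission and leaves the primary outcomes inside it.

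A reader might go further and infer that 5-year values will be created for children who died, because the imputation sentence is unqualified, all analyses are intention-to-treat, and the *Safety* section says "Severe adverse events (SAEs) may be defined as death". The documents do not support that. The *Safety* wording classifies events and says nothing about analysis. A blood pressure after death can be read as undefined, not missing. A condensed article may leave the handling of deaths to the full protocol or analysis plan. Nor does a survivors-only primary estimate follow: the *Background* section cites a possible effect of the diet on mortality, so survival to 5 years may itself depend on the arm.

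**Conclusion.** The point holds in a limited form. As written, the plan allows a 1-year, or arguably a 2-year, blood pressure or glucose value to be analysed as the 5-year primary value. It has no such reach for distensibility. The remark in the analysis section about change from baseline might suggest an earlier distensibility value, but none is listed.

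The consequence is conditional. It is bias if carried-forward shares differ by arm or if the early effect differs from the 5-year effect, and otherwise a loss of power compared with complete data. Under the assumed 5 to 8 mmHg rise, a 10-point difference in shares gives 0.5 to 0.8 mmHg under the null, in either direction. Equal 20% shares with no early effect turn 3.0 into 2.4 mmHg. Shares of 15% and 25% with no early effect give −1.75 to −3.05 against a true −3.0, depending on which arm loses more. The real size cannot be known from the documents, which give no missingness rate and no 1- or 2-year levels. It would overstate the case to say that the primary comparison will be biased.

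**What to change.** Delete the last-value-carried-forward sentence, or at the least exclude the 5-year outcomes from it. State that missing 5-year values are handled by the chained-equations multiple imputation already specified. Its predictors should include randomized arm, the 1- and 2-year blood pressure and glucose values, and baseline variables. The early measurements then inform the 5-year value without standing in for it, and all three primary outcomes fall under one rule.

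The cost is a wording change, slightly more analysis work, and somewhat wider but more honest intervals. No new data are needed. The change should be made before any 5-year outcome data are examined.
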